### Eligibility criteria

A total of 40 patients with CCH will be included in the study and have a full ONS system implanted. The diagnosis is confirmed after a thorough neurological assessment based on the criteria listed in the *International Classification of Headache Disorders, 3. Edition (ICHD-3)* [1], see Table 1 and Table 2.

**Table 1 Tab1:** Diagnostic criteria for cluster headache

A. At least five attacks fulfilling criteria B-D
B. Severe or very severe unilateral orbital, supraorbital, and/or temporal pain lasting 15–180 min (when untreated)
C. Either or both of the following
1. At least one of the following symptoms or signs, ipsilateral to the headache:
• Conjunctival injection and/or lacrimation
• Nasal congestion and/or rhinorrhea
• Eyelid edema
• Forehead and facial sweating
• Miosis and/or ptosis
2. A sense of restlessness or agitation
D. Occurring with a frequency between one every other day and 8 per day
E. Not better accounted for by another ICHD-3 diagnosis

**Table 2 Tab2:** Chronic cluster headache

A. Attacks fulfilling criteria A-E for Cluster headache, and criterion B below
B. Occurring without a remission period, or with remissions lasting < 3 months, for at least one year

*ICHD-3* International classification of headache disorders 3^rd^ edition

In addition to meeting the ICHD-3 criteria for CCH, participants must also comply with the study eligibility criteria listed in Table 3.

**Table 3 Tab3:** Eligibility criteria

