**Fig. 2 Fig2:**
[figure not shown]
Outcome parameters in correlation to trial phases and study visits. TENS, transcutaneous electrical nerve stimulation. ONS, occipital nerve stimulation. PGIC, patient's global impression of change. HADS, hospital anxiety and depression scale. EuroQoL-5D, European Quality of Life – 5 Dimensions

All questionnaires are electronic and are entered via a personal link sent automatically by e-mail. If the headache registrations and questionnaires are not completed within 24 h, an e-mail reminder is generated.

The data collected during each trial phase will be compared to the baseline and analyzed in order to evaluate the study endpoints listed in Table 4.

**Table 4 Tab4:** Study endpoints

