### Sample size

Based on our previous experience with ONS treatment [26], we estimate that 50% of the participants who receive active treatment with burst ONS will reach the primary endpoint of a 30% reduction in attack frequency. A blinded trial with burst ONS and placebo has to our knowledge not been carried out earlier, but we hypothesize that no more than 10% in the placebo group will meet the primary endpoint [35]. The sample size is calculated using Fisher’s Exact test based on the above-mentioned assumptions and with 80% power (two-tailed) and a α = 0.05, a total of 40 participants (20 in each allocation group) are needed to be enrolled in the study and an ONS-system implanted.

Each enrolled participant contributes their data regardless of whether they complete the project or not. In case of participants excluded after enrollment, the reason for exclusion will be described.

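### The stated 80% power is about 74% by the named Fisher's exact test at 50% v 10%, and it falls quickly if placebo response exceeds the assumed 10%

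*Protocol article*

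**What the plan says.** All planning inputs are in the Sample size section of the protocol article. For the active arm: "we estimate that 50% of the participants who receive active treatment with burst ONS will reach the primary endpoint". For the control arm: "we hypothesize that no more than 10% in the placebo group will meet the primary endpoint", a figure for which the article cites reference 35. The same sentence notes that, to the authors' knowledge, burst ONS has not been compared with placebo in a blinded trial. The method is named: "The sample size is calculated using Fisher’s Exact test", "with 80% power (two-tailed) and a α = 0.05". The result is that "a total of 40 participants (20 in each allocation group) are needed". No other placebo rate and no range is shown.

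Three design facts bear on the placebo rate.
- The endpoint is a 30% fall in attack frequency. For its reference, the Outcome measures section says: "The data collected during each trial phase will be compared to the baseline". That baseline lasts four weeks and comes before 12 weeks of TENS; the blinded phase lasts 12 weeks (Abstract, Methods).
- Table 3 sets a floor of 15 attacks per month, and Table 1 allows up to 8 per day.
- Table 2 defines the chronic form as "Occurring without a remission period, or with remissions lasting" less than three months, so attack-free stretches are compatible with eligibility.

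**The concern.** Two things look wrong with the power statement. First, 20 per arm is small for an exact test at 50% v 10%. Fisher's test is conservative at this size, so a total of 40 looks like the result of a different calculation from the one named.

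Second, the power is quoted at a single control rate that is described as a ceiling. A placebo responder is anyone whose 12-week frequency is at least 30% below a short baseline count. Counting noise, natural fluctuation, a remission, a lasting effect of TENS or a true placebo response can all produce one, and the 10% has to cover them together.

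At stake is how the randomised comparison is read. Every participant undergoes implantation, and a reader who takes 80% at face value will give a non-significant result more weight than the design supports.

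**Working it through.** **Step 1: the plan's own figure.** Inputs, all from the Sample size section: p1 = 0.50, p2 = 0.10, two-sided alpha 0.05, 20 per arm.

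*Named test.* Enumerate every pair (x, y) of responders out of 20 and 20. Power is the sum of Bin(x; 20, 0.50) × Bin(y; 20, 0.10) over pairs with a two-sided Fisher p ≤ 0.05. For illustration, 8 v 2 responders gives p = 0.065 and 9 v 2 gives p = 0.031. The results:

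| Per arm | 20 | 21 | 22 | 23 |
|---|---|---|---|---|
| Fisher power | 74.2% | 75.9% | 78.6% | 81.1% |

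So 80% needs 23 per arm, 46 in total.

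*Where 40 comes from.* The uncorrected normal approximation gives

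n = [1.96·√(2·0.3·0.7) + 0.8416·√(0.5·0.5 + 0.1·0.9)]² / 0.4² = (1.270 + 0.491)² / 0.16 = 19.4, rounded up to 20 per arm.

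Its power at 20 per arm is 81.3%. The Pearson chi-square test gives 83.8% by enumeration. With a continuity correction the formula gives 25 per arm. The stated 40 therefore fits an uncorrected calculation and not two-tailed Fisher.

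**Step 2: sensitivity to the placebo rate.** Fisher, 20 per arm. The documents do not say what happens to the burst rate if background response is higher than planned, so three readings are shown:
- (a) burst stays at 50%;
- (b) background and treatment act independently, so burst = 1 − (1 − q)·(0.5/0.9) for placebo rate q;
- (c) the 40-point difference is kept.

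| Placebo rate q | (a) burst 50% | (b) independent | (c) 40 points kept |
|---|---|---|---|
| 5% | 89% | – | – |
| 10% | 74% | 74% | 74% |
| 15% | 57% | 64% | 70% |
| 20% | 41% | 55% | 65% |
| 25% | 27% | 45% | 61% |
| 30% | 16% | 37% | 60% |

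**Step 3: responders with no effect at all.** Simulate a 4-week count and a 12-week count with the same expected weekly rate, and take the share with a follow-up rate at most 0.7 times baseline. The mean rates are illustrative. The period-to-period fluctuation of the true rate (log-SD) is an assumption; the documents give none.

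| Mean attacks per 4 weeks | Poisson noise only | log-SD 0.2 | log-SD 0.3 | log-SD 0.4 |
|---|---|---|---|---|
| 14 (about the entry floor) | 10.8% | 19% | 24% | 29% |
| 20 | 7.2% | 17% | 23% | 28% |
| 30 | 3.7% | 15% | 22% | 27% |
| 60 | 0.6% | 13% | 21% | 27% |

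On remissions: 3.6 attack-free weeks out of 12 is already a 30% fall (0.3 × 12 = 3.6). If 10% of patients had a remission of 2 to 12 weeks (also an assumption), Poisson noise plus remission gives 9 to 15% at means of 20 to 60.

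The no-effect share thus runs from about 1% to about 29%, depending on attack rate and assumed fluctuation.

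**The case against.** The strongest reply is that the 10% is a cited assumption. Its source is not at hand, and the remark that no blinded burst trial exists does not mean that no placebo-response data exist. This stands: 10% is untested for this design, not refuted.

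A reader might infer that the endpoint's construction alone pushes placebo response above 10%. The documents do not support that. They give no within-patient variability, no remission frequency and no mean attack rate. Only a patient close to the entry floor reaches 10.8% from counting noise; at 20 to 60 attacks per 4 weeks, noise alone gives 7.2% down to 0.6%. If placebo response were 5%, Fisher power would be 89%, above the stated figure. Any range shown must therefore extend below 10%.

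A reader might also infer that a null result becomes the likelier outcome at 20% placebo response. That holds only with burst fixed at 50% (41%). Fluctuation, remission and TENS carry-over act on both randomised arms. If the planned 50% does not already contain that background, power at 20% is 55 to 65%. The loss is then smaller, but power is still well short of 80%.

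Finally, rules for reporting a non-significant result commonly belong in an analysis plan, so their absence from an article is no fault. None of these replies touches Step 1, which uses only the article's own inputs and its named test.

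**Conclusion.** The firm part is an arithmetic mismatch that needs no outside assumption. At 50% v 10% with 20 per arm, two-tailed Fisher's exact test has 74.2% power, not 80%; the named test needs 46 participants in total.

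The second part is a conditional statement. Power depends steeply on the placebo rate: from 89% at 5% to 16% at 30% with burst held at 50%, and 55 to 65% at a 20% placebo rate if background response lifts both arms. The design can generate responders without any effect, but whether these exceed 10% depends on variability that the documents do not report. The 10% may be too low; it is not shown to be wrong.

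The two parts should not be confused. Most of the gap between 80% and about 70% comes from the test mismatch: moving the placebo rate from 10% to 11% takes Fisher power only from 74.2% to 70.9%.

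**What to change.** In the Sample size section, restate the power of 40 participants as about 74% for 50% v 10% by two-tailed Fisher's exact test. Next to it, show power over an assumed placebo range: 89, 74, 57, 41, 27 and 16% at 5, 10, 15, 20, 25 and 30%. State that burst is held at 50% and that the range is an assumption.

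The cost is wording only. No added patients are needed and no procedure changes; the printed power becomes less favourable.

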**Exclusion criteria**
• Other ongoing neuromodulation therapies
• Current alcohol and/or drug abuse
• Known severe psychiatric disorders
• A concomitant second type of chronic primary or chronic secondary headache (e.g., chronic migraine or chronic post-traumatic headache, while chronic tension-type headache is allowed)
• Major posterior cervical surgery at C3-level and above
• Pregnancy
• Treatment with oral steroids and/or GON block 30 days before study enrollment

During the trial, the participants may continue their usual preventive and abortive headache medication, but they cannot have any dose increase of their current medication or start new preventive medication. Neither can the participants receive any interim treatment such as GON blocks (with injected steroids and/or local anesthetics) or high-dose oral prednisolone after enrollment. In this case, the participant will be withdrawn from the study. A reduction in medicine dose or discontinuation of a drug is allowed.

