## Methods: assignment of interventions

### Randomization and blinding

After the 14-day grace period following ONS implantation, the ONS systems will be programmed and the participants will be allocated 1:1 in the two study groups (burst ONS or placebo). The allocation is conducted by block randomization with blocks of random size between four and eight, using a specially designed automated electronic randomization tool. The allocation tables for the randomization are inaccessible to the investigators and other staff involved in the project.

The randomization is performed by the implanter or the project nurse who is responsible for the programming of the ONS systems. These personnel are unblinded throughout the entire trial and are therefore able to handle any ONS-related events during the blinded trial phase without mitigating the blinding. Unblinded personnel will not have any role in data collection, management, and analysis.

The participants are blinded to their allocation group. The principal investigator and other study personnel who perform the evaluation of outcome parameters, are blinded to the allocation group as well, and will not have access to the randomization tool in the project database. Blinding is maintained until all participants have completed the final trial phase.

The IPGs used in the study are non-rechargeable units to ensure that a lack of need for recharging does not unblind the participants. In addition to this, to avoid accidental unblinding, the participants will not have the remote controls to the ONS system during the blinded trial phase, since the display would reveal if stimulation is on. Importantly, when treated with burst stimulation, participants should not have any sensation of stimulation and, hence will not need to adjust the stimulation amplitude. The postoperative 14-day grace period ensures accurate programming, which in our experience limits the need for stimulation adjustments within the 12 weeks of blinded trial to an absolute minimum. If needed, patients can directly contact the principal investigator. Should the participants get a sensation of stimulation during the blinded trial phase, unblinded personnel can adjust the stimulation settings if necessary.

When crossing over to the open-label tonic ONS trial phase, all participants are equipped with a remote control.

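### The 80% power is printed for 40 participants counted at enrolment and implantation, with no allowance for losses before the blinded-phase outcome; the named Fisher test gives about 74% at 20 + 20 even with none

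*Protocol article*

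**What the plan says.** The Sample size section sets the design inputs: "we estimate that 50% of the participants who receive active treatment with burst ONS will reach the primary endpoint", "we hypothesize that no more than 10% in the placebo group will meet the primary endpoint", and "The sample size is calculated using Fisher’s Exact test", with two-tailed α = 0.05 and 80% power. From these it concludes that "a total of 40 participants (20 in each allocation group) are needed to be enrolled in the study and an ONS-system implanted". The Eligibility criteria section uses the same number: "A total of 40 patients with CCH will be included in the study and have a full ONS system implanted".

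Randomisation comes later. The Abstract gives four weeks of baseline, 12 weeks of TENS, implantation, a two-week grace period and then the 12-week blinded phase. The Randomization and blinding section confirms the order: "After the 14-day grace period following ONS implantation, the ONS systems will be programmed and the participants will be allocated 1:1".

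The article expects some participants to leave. After a prohibited medication change or interim treatment, the text below the exclusion criteria says "In this case, the participant will be withdrawn from the study". Participant information gives the right to stop at any time and lists surgical and device complications. The Sample size section adds "In case of participants excluded after enrollment, the reason for exclusion will be described". No loss rate, inflation or replacement rule is printed next to the power statement. Patient recruitment says only that recruitment goes on until the sample size is reached.

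**The concern.** One number, 40, stands for patients included, patients implanted and the 20 + 20 that the power calculation compares. These groups coincide only if nobody leaves between the counting point and the end of the blinded phase. A participant who leaves before randomisation cannot supply a burst-versus-placebo outcome, whatever the analysis principle.

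At stake is how a null result would be read. The Discussion presents this as the first randomised, blinded, placebo-controlled trial of ONS in chronic cluster headache. A non-significant burst-versus-placebo result from a trial described as having 80% power would carry more weight against burst ONS than the design supports. Readers would take the chance of missing a 50% versus 10% difference as one in five, when it is about one in four with complete data and about one in three at 18 per arm.

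**Working it through.** **Inputs.** From Sample size: burst 0.50, placebo 0.10, two-sided α 0.05, target power 0.80, 20 per arm, Fisher's exact test. From the Abstract: 4, 12, 2 and 12 weeks. Loss rates of 5% to 20% are an assumption, because the article gives none.

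**1. Time at risk.** Enrolment to randomisation: 4 + 12 + 2 = 18 weeks at least. Enrolment to the end of the blinded phase: 18 + 12 = 30 weeks at least. Implantation to the end of the blinded phase: 2 + 12 = 14 weeks.

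**2. Where 40 comes from.** The normal-approximation formula with pooled variance and no continuity correction is

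n = [1.96·√(2·p̄·(1 − p̄)) + 0.8416·√(p1(1 − p1) + p2(1 − p2))]² / (p1 − p2)²

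with p̄ = (0.5 + 0.1)/2 = 0.3. This gives [1.96·√0.42 + 0.8416·√0.34]² / 0.16 = 19.4, so 20 per arm and 40 in total, with approximate power 81.3%. The printed 40 therefore matches the uncorrected normal formula. It does not match the test that the section names.

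**3. Exact power of the named test.** Every pair (x, y) of responder counts is enumerated and Bin(x; n1, 0.5) × Bin(y; n2, 0.1) is summed over the pairs with two-sided Fisher p ≤ 0.05.

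| Per arm | Balanced loss from 20 | Fisher power | Uncorrected normal |
|---|---|---|---|
| 20 | 0% | 74.2% | 81.3% |
| 19 | 5% | 70.9% | 79.2% |
| 18 | 10% | 66.8% | 76.8% |
| 17 | 15% | 62.6% | 74.2% |
| 16 | 20% | 58.1% | 71.4% |

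Fisher power is 78.6% at 22 per arm and first passes 80% at 23 per arm (81.1%), a total of 46.

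**4. Losses after randomisation counted as non-responders.** With 20 per arm kept and a loss fraction d in both arms, the rates become 0.5(1 − d) and 0.1(1 − d). At d = 5, 10, 15 and 20%, Fisher power is 70.3, 66.2, 62.0 and 57.6%, close to the balanced-loss figures above.

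**5. Unbalanced losses.** Fisher power does not fall steadily with n. With burst listed first: 19 + 20 gives 79.7%, 20 + 19 gives 75.9%, 18 + 20 gives 75.3% and 20 + 18 gives 76.4%, all above the 74.2% at 20 + 20. On the uncorrected normal formula, one loss leaves 80.4% (19 + 20) or 80.1% (20 + 19).

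**6. Separating the two effects.** The gap with no loss is 80 − 74.2 = 5.8 points and has nothing to do with attrition. A balanced 10% loss takes a further 74.2 − 66.8 = 7.4 points, or 74.2 − 66.2 = 8.0 points under the non-responder count.

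**The case against.** A reader might infer that the plan enrols exactly 40 people 18 weeks before randomisation, so that every departure in baseline or TENS eats into the 20 + 20. The text does not support that well. Both statements of the number join inclusion with implantation, and recruitment continues until the sample size is reached. The better reading is 40 implanted, which already covers the 16 weeks before surgery. The grace period and the blinded phase stay uncovered on either reading, and the wording leaves the counting point unsettled.

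A reader might also infer that the 80% holds as long as nobody is lost, or that any loss lowers power. Neither is right. Under the named test 80% is not reached even with complete data. Under the formula that yields 40, one loss still leaves just over 80%. A single loss from one arm raises exact Fisher power slightly.

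Further, the article says that every enrolled participant contributes data, attack counts are collected weekly with automatic reminders, and the primary analysis is by intention to treat. Someone who leaves midway through the blinded phase may therefore have usable weeks, and missing-data handling can properly sit in a fuller document. This stands: it may soften losses after randomisation, and it is why the loss figures are illustrations, not forecasts. It does nothing for a participant lost between implantation and randomisation, and it does not repair the 74.2%.

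**Conclusion.** The point holds in this form: the printed 80% is attached to a count taken before randomisation, carries no allowance for loss over about 14 weeks, and is not delivered by the named test at 20 + 20. The no-loss figure of 74.2% uses only the article's own inputs. The figures of about 67% at 18 + 18 and about 58% at 16 + 16 rest on assumed balanced losses of 10% and 20%. The direction does not depend on the choice of test, since the uncorrected normal formula also falls to 76.8% and 71.4% at those sizes. Attrition should not be charged with the whole distance from 80%: at a 10% balanced loss its share is 7 to 8 points, and the other 5.8 points come from the mismatch between the test named and the formula that gives 40. The matter is worth correcting, but it does not undermine the randomised comparison itself.

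**What to change.** In Eligibility criteria and Sample size, state that the target of 40 (20 per arm) is counted at randomisation and that participants who leave earlier do not count toward it. Replace the flat 80% with the exact two-sided Fisher power: about 74% with complete data and about 67% under a balanced 10% loss, with the 10% labelled as an assumption.

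For the burst-versus-placebo comparison only, define the analysis set as all randomised participants. This limit matters because reduction in attack frequency with TENS is also a primary endpoint and TENS precedes randomisation. All participants who start TENS should stay in the TENS analysis.

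The cost is a less favourable printed power and possibly a few more participants going through baseline and TENS, or through implantation to replace those lost in the grace period. If no replacement is wanted, restating the power alone is sufficient and adds nobody. Keeping 80% with the named test would take 46 participants with an outcome, six more than planned; that is a larger change and is not needed to make the statement correct.

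### Twenty per group gives 74% power, not 80%, with the Fisher's exact test that the sample-size section names

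*Protocol article*

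**What the plan says.** All inputs are in the Sample size section of the protocol article:

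- Active arm: "we estimate that 50% of the participants who receive active treatment with burst ONS will reach the primary endpoint of a 30% reduction".
- Placebo arm: "we hypothesize that no more than 10% in the placebo group will meet the primary endpoint".
- Test: "The sample size is calculated using Fisher’s Exact test based on the above-mentioned assumptions".
- Operating characteristics: "with 80% power (two-tailed) and a α = 0.05".
- Result: "a total of 40 participants (20 in each allocation group) are needed to be enrolled in the study".

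The Randomization and blinding section confirms 1:1 allocation. The sample-size section adds no allowance for losses and says only that "Each enrolled participant contributes their data regardless of whether they complete the project or not". The calculated number and the number to be implanted are therefore both 40.

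**The concern.** With every input stated, the calculation can be repeated exactly. Fisher's test conditions on the total number of responders and is conservative in small samples, so it usually needs more patients than the ordinary chi-square formula. A round 20 per group at 50% versus 10% looks like the chi-square answer under Fisher's name.

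The article presents the trial as the first randomized, blinded, placebo-controlled trial of ONS in chronic cluster headache, and every participant receives an implant. A null result would be read against the stated 80% power. If the true figure is lower, such a result would be given more weight than it deserves.

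**Working it through.** **Inputs.** p1 = 0.50, p2 = 0.10, n = 20 per arm, two-sided alpha = 0.05, target power 0.80, all from the Sample size section.

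**Where 20 comes from.** The uncorrected chi-square (pooled normal) formula is

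n = [z(0.975)·√(2·p̄(1−p̄)) + z(0.80)·√(p1(1−p1) + p2(1−p2))]² / (p1−p2)², with p̄ = 0.30.

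n = [1.960·√0.42 + 0.842·√0.34]² / 0.16 = (1.270 + 0.491)² / 0.16 = 19.4, so 20 per group.

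This reproduces the plan's figure, but for a different test. The continuity-corrected version, which approximates Fisher, is (19.38/4)·[1 + √(1 + 4/(19.38·0.4))]² = 24.1, so 25 per group.

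**Exact power of the named test.** Power is the sum, over all 21 × 21 outcomes with Fisher two-sided p ≤ 0.05, of Binomial(20, 0.5) × Binomial(20, 0.1) probabilities. The table gives, for each placebo count, the smallest burst count that is significant. Results favouring placebo add a negligible amount.

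| Placebo responders | Probability at 10% | Burst responders needed | Probability at 50% | Product |
|---|---|---|---|---|
| 0 | 0.1216 | ≥ 5 | 0.9941 | 0.1209 |
| 1 | 0.2702 | ≥ 7 | 0.9423 | 0.2546 |
| 2 | 0.2852 | ≥ 9 | 0.7483 | 0.2134 |
| 3 | 0.1901 | ≥ 10 | 0.5881 | 0.1118 |
| 4 | 0.0898 | ≥ 11 | 0.4119 | 0.0370 |
| 5 | 0.0319 | ≥ 13 | 0.1316 | 0.0042 |
| 6 | 0.0089 | ≥ 14 | 0.0577 | 0.0005 |
| Total | | | | **0.7424** |

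Doubling the one-tailed p-value gives the same 0.7424, so the choice of two-sided convention does not matter.

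**Size needed with Fisher.** Power by n per group is 0.742 (20), 0.759 (21), 0.786 (22), 0.811 (23) and 0.834 (24). The first size to reach 80% is 23 per group, 46 in total.

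**Why Fisher falls short.** At 20 versus 20 its actual two-sided type I error is at most 2.5% (maximum 0.0253 over all common response rates), about half the nominal 5%.

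**Sensitivity of Fisher's test at 20 per group, burst rate 50%.**

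| Placebo rate | Power |
|---|---|
| 5% | 89.4% |
| 8% | 80.6% |
| 9% | 77.5% |
| 10% | 74.2% |
| 15% | 57% |
| 20% | 41% |

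If 10% of each arm were lost and counted as non-responders (45% versus 9%), power would be 66%. Both the loss rate and the counting rule are assumptions; the article gives neither.

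**An exact alternative at the same size.** Boschloo's test orders tables by the Fisher p-value and maximises the tail probability over the unknown common rate. For 0 to 6 placebo responders, the burst counts needed become 5, 6, 8, 9, 11, 12 and 13. Power at 50% versus 10% is 0.822 and the maximum type I error is 0.046. For example, 9/20 versus 3/20 gives p = 0.082 with Fisher and p = 0.042 with Boschloo.

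**The case against.** The arithmetic is not in dispute. The case on the other side concerns how much it matters.

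- **Fisher is named only for planning.** The Statistical analysis section names a Wilcoxon signed-rank test against baseline for the primary outcome and no two-arm responder test. This stands: the 26% risk applies if Fisher is the test used. The proven error is that 40 does not follow from the stated inputs.
- **The placebo figure is a ceiling.** At 8% or below, Fisher does reach 80%. But 10% is the only planning rate given, and a size based on a ceiling must hold at that ceiling.
- **The gap is small.** It is 5.8 points of power, or six patients, and it does not affect bias or type I error. That is fair, and it is why the correction can be confined to the text.
- **Higher placebo rates are speculative.** The blinded phase follows 12 weeks of TENS and surgery, yet response is judged against the earlier baseline. As an illustration, suppose attacks are Poisson at the entry minimum of 15 a month, and a 4-week baseline is compared with 12 weeks. About 11% of unchanged patients would then show a 30% fall by chance. At 30 attacks per 4 weeks this drops to 3.7%, and at 60 to 0.6%. The article gives no attack distribution, so this does not show that the placebo rate exceeds 10%. It only shows that 10% should not be treated as a safe maximum.
- **Choosing Boschloo because it restores 80% fits the test to the number.** There is some force in this. It is legitimate only if fixed before unblinding. The article allows that, since blinding lasts until all participants finish the final phase and no interim analysis is planned.

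**Conclusion.** The stated power is wrong for the named test. With 20 per group, 50% versus 10%, and two-sided Fisher at 0.05, power is 74.2%, a shortfall of 5.8 points. The same test needs 46 patients for 80%. This result uses only figures in the Sample size section and no added assumption. The most likely cause is that a chi-square formula was used and labelled as Fisher's exact test, though the article does not show which formula was run. The consequence for the trial, a type II risk of 26% rather than 20%, is conditional on Fisher being used for the between-arm comparison. The loss and Poisson figures are illustrations and the verdict does not rest on them.

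**What to change.** Before unblinding, make one of these changes in the sample-size text and carry the same test into the analysis section:

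1. Preferred: name Boschloo's unconditional exact test for the burst-versus-placebo responder comparison, and state that 20 per group gives 82% power at 50% versus 10%. The test is exact, is uniformly more powerful than Fisher and supports the stated 80% at the planned size.
2. If Fisher is kept: restate the power for 40 participants as 74%.

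If the 40 in fact came from the uncorrected chi-square formula, the text should say so, whichever analysis test is chosen. In either case, add the power at placebo rates of 15% and 20% for the chosen test; for Fisher these are 57% and 41%.

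The cost is about one sentence in each section and no additional patients. Under the second option the published power becomes somewhat less favourable.
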